##### Self-referential processing

This study will explore if decentering training influences the ability to flexibly shift one’s self-perspective. This can be indexed using the own-body transformation task (online supplemental figure S2).^49^ On each trial, a schematic human figure is presented that face either with their front to the participant or their back to the participant. This figure also holds a black glove in one hand (eg, left). Participants are instructed to imagine themselves in the body position of the figure and then judge whether the glove is held by the figures left of right hand. Performance is compared with a within-subject control task wherein participants judge the position of the glove without altering their self-representation. The outcome variables are mean RT and the percentage error rate. These are found to increase as a function of the self-perspective manipulation; that is, they are higher for front-facing characters.

10.1136/bmjopen-2021-056864.supp3Supplementary data

### Procedure

#### Data quality

Checks of data quality will be included ad different stages of data collection and analysis. First, ‘catch questions’ will be embedded in self-report assessments to assess whether participants actively read questions (eg, ‘Please select "Not at all"’). Second, participants self-rate the quality of their data at the end of each data collection period, for example, []. Piloting revealed this to be a useful strategy. Third, all the standard markers of appropriate behavioural performance will be checked when analysing task data (eg, RTs>250 ms and <3000 ms; chance-level accuracy).

#### Assignment of interventions

##### Allocation

Following baseline assessment, participants will be stratified according to sex and depression severity (using the CES-D). They will then be randomly assigned to either the decentering training programme or the active control condition. This will be managed by the trial statistician (PW) using a minimisation procedure. Participant allocation will be then shared with the research coordinator responsible for providing appropriate access links for the online intervention ([name], [name] and HC).

##### Blinding

Research coordinators ([name] and [name]) will be blinded during assessment, data preprocessing and statistical analysis. Due to the nature of the study, it is not possible to remain blinded during participant allocation. This is because each participant needs to be given a secure link to the online training programme, either decentering training or the active control. All outcome assessments will be completed online; participants will access the same link to complete online assessments, regardless of group. Thus, there are no in-person data collectors with an awareness of participants’ allocation. Initial data will be preprocessed (eg, calculation of summary scores like means, percentage accuracy, sums, etc). Preprocessing will be completed using pre-existing scripts coded in R and MATLAB ([name]). At this point, the dataset will be shared with the trial statistician (PW) who will conduct the statistical analysis and who will be blind to participant allocation. Once the analysis is complete, the trial coordinators will unblind the dataset by indicating which participants were allocated to which group.

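### The research coordinator role receives the allocation, provides the arm-specific links and reveals allocation at the end, yet is declared blind in between, so blinded preprocessing is not secured as described

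*Protocol article*

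**What the plan says.** In the protocol article, under Allocation, the trial statistician manages the minimisation, and the result is passed on: "Participant allocation will be then shared with the research coordinator responsible for providing appropriate access links for the online intervention". Three people are listed for this task.

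The Blinding section opens with a statement about the same role, this time listing two people: "Research coordinators ([name] and [name]) will be blinded during assessment, data preprocessing and statistical analysis". An exception follows directly: "Due to the nature of the study, it is not possible to remain blinded during participant allocation". The reason given is that "each participant needs to be given a secure link to the online training programme, either decentering training or the active control".

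The section then describes how data are handled. Assessments are online, and "participants will access the same link to complete online assessments, regardless of group". On scoring it says "Preprocessing will be completed using pre-existing scripts coded in R and MATLAB", with one person listed. After the analysis, "the trial coordinators will unblind the dataset by indicating which participants were allocated to which group".

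The Data quality section describes three kinds of check. Catch questions are embedded in the self-report forms; "participants self-rate the quality of their data at the end of each data collection period"; and standard performance markers are applied to the cognitive task data.

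**The concern.** A person can be blind at a late stage of a trial only if they never learned the arm, or if they cannot connect what they learned to the record in front of them. The article declares a role blind for preprocessing and analysis after giving that role the allocation at the start, and it describes nothing that would meet either condition.

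The stake is modest but real. The Experiences Questionnaire, the symptom and well-being scales and the experience-sampling items are all self-reports from participants who spend five weeks on one programme or the other. Masked data handling is therefore one of the few protections of the comparison that the trial team controls. If someone who knows the arm decides whether a doubtful record stays in, the decision can lean without any intent. The trial report would also repeat a blinding statement that the described arrangements do not support.

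**Working it through.** No arithmetic applies beyond the sample size: 57 per group × 2 groups = 114 participants, whose allocation passes to the coordinator role. The check is to set the sections side by side and follow who knows what, and when.

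1. **Start of the trial.** Under Allocation, the coordinator responsible for the links is told each participant's arm. Under Blinding, the need to issue an arm-specific link is the stated reason why masking fails at this step. The two sections agree that the link-issuing role is unblinded from allocation onwards.

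2. **Middle of the trial.** The opening sentence of Blinding declares the research coordinators masked at assessment, preprocessing and analysis. All three come after allocation for every post-randomisation record.

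3. **End of the trial.** Coordinators unblind the finished dataset by stating who was in which group. To do this they must have had access to the key until then.

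4. **What could reconcile 1 and 3 with 2.** There are two possibilities.
   - *Different people.* Those who issue links and hold the key might not be those who handle data. No such division is stated. Allocation lists three people, Blinding lists two as masked, and one person runs the scripts. Most of these names are masked, so the lists cannot be compared person by person.
   - *Different identifiers.* Records might be re-coded before preprocessing so that the allocation list no longer matches. None is described. Under Consent and data collection, the trial identification code is what goes on the list for allocation. Under Data confidentiality and management, the same code is used to submit assessments. The code that links a participant to an arm is thus also on the outcome data.

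5. **A further route to knowledge of the arm.** The Intervention and Participant retention sections plan contact before week 1 and in week 3 to discuss experience of the programme. The caller's role is not stated, but whoever calls is likely to learn the arm.

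6. **Where knowledge of the arm could act.** Taking the handling steps in turn:
   - Outcome collection: online, one link for both arms, no in-person collector. Coordinators rate nothing, so there is little room.
   - Scoring: summary scores from scripts that already exist. Little room.
   - Missing items: a total is calculated if less than 20% of a measure is missing. Fixed.
   - Experience sampling: at least 33% of questionnaires completed. Fixed.
   - Response-time limits of 250 ms and 3000 ms, and chance-level accuracy: these concern task data, which are exploratory.
   - Failed catch questions and poor self-rated data quality: the article does not say what follows from either. This is the only place in the self-report data where discretion may remain.

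**The case against.** The strongest reply is that the sections are loosely worded rather than inconsistent in practice. The exception is impersonal: it says that blinding cannot be kept at allocation, not that the two people listed as masked are the ones who send links. Allocation speaks of a single responsible coordinator, and one of its three entries is shown by initials that do not appear in the Blinding list. At least one link-issuer is thus apparently outside the group declared blind, and a workable separation may exist behind the masked names. Scoring is scripted, the main inclusion thresholds are fixed, and the Dissemination section commits to publishing the anonymised data and the processing scripts, so the cleaning can be audited. A condensed article may also leave the handling of catch questions to a fuller document.

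Much of this stands. It limits the size of the problem, and it rules out a stronger reading that a reader might infer: that the very people who send the links also clean the data, so that there is no blinded cleaning at all. The documents do not show this, because the overlap is one of role and not of person. Nor do they support the inference that exclusions from the primary outcome will be steered by arm. Data quality assigns its checks to nobody in particular and does not say that a failed check leads to exclusion.

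The reply does not remove the conflict itself. The article affirmatively claims blinding for a role that it elsewhere makes the recipient and discloser of the allocation. That is a contradiction in the text, not a detail left to another document. Publishing the scripts shows the final rules, but not whether they were set before anyone who knew the arms had seen the data.

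**Conclusion.** The point holds in limited form. The Allocation and Blinding sections conflict on the coordinator role, and nothing described would restore blinding after allocation. The accurate description is that blinded preprocessing is not secured, not that it is shown to be absent.

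The likely bias is small and cannot be quantified from the article. The allocation of all 114 participants is known to the role, but that knowledge can affect the self-report data only where a decision about a failed catch question or a poor quality self-rating is left to judgement. How many such records there will be is not stated.

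This rests on two assumptions: that the coordinator role means the same thing in both sections, and that no separation of staff or re-coding exists that the article leaves unmentioned. If one does exist, a sentence stating it settles the matter. The correction is still worth making, because the blinding statement would carry into the trial report and the remedy costs almost nothing. The trial statistician's double part in minimisation and masked analysis is a separate question, and this conclusion does not rely on it.

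**What to change.** Reconcile the two sections as follows.

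- State under Blinding that coordinators who issue links or hold the allocation key are unblinded from allocation onwards, and remove the claim that they are blind during preprocessing and analysis.
- Assign scoring and data-quality exclusions to an existing team member who neither issues links nor makes the calls before week 1 and in week 3. That person should work on a file without allocation and have no access to the allocation list.
- Write down what follows from a failed catch question and from a poor self-rating of data quality. Freeze those rules and the preprocessing scripts, with a date, before any post-randomisation data are opened.

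The cost is a minor reassignment of tasks within the team and a dated freeze of scripts that already exist. No extra staff, participants or assessments are needed.

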#### Consent and data collection

Recruited volunteers will complete an eligibility check during an initial phone call. Volunteers who are eligible will be invited to participate in the study. Written informed consent will be sought after an initial briefing that explains the data collection protocol (see online supplemental appendix B for consent form). This briefing will also include a tutorial on downloading and using the experience sampling app (PsyMate2; www.psymate.eu). Participants will also have the opportunity to ask any questions. To discourage possible contamination, participants will be asked to keep the content of the study confidential from others. Once consent is provided, participants will be given an anonymous trial identification code and added to an encrypted list for allocation. Participants will also receive a URL link to complete baseline measures. Figure 1 illustrates the full schedule for outcome measures. Participants will receive a tutorial on accessing the intervention materials.

10.1136/bmjopen-2021-056864.supp4Supplementary data

Over 5 weeks, participants in both interventions will access and rehearse exercises (Monday–Friday). Decentering training exercises are based on audio files to be delivered via their preferred music/poststreaming services (eg, Spotify/Podcast Addict). The active control exercises are based on YouTube videos posted on a Private Channel. Each day, the PsyMate2 App will prompt participants to complete their daily exercise as well as complete any required ESM items. These will be sent four times per day. A brief survey will also be sent through email each evening to ask whether participants completed their daily exercises, and if so, to ask about their experiences as well as questions on their mood states. At the end of week 5, participants will be asked to complete the online assessment battery. Participants will then complete a debriefing session. During the debriefing session, they will be given the opportunity to provide feedback on their experience of the study, and to ask any questions they may have. They will also be given a list of relevant mental health resources should they feel the need to access them.

#### Participant retention and follow-up

Retention will be promoted in a number of ways. First, participants will not be paid until receipt of their completed postintervention assessment battery. Second, participants will be made aware that they can receive a bonus payment of £20 if they complete all of their assessments and daily diaries. Third, telephone contact will be made with participants prior to week 1 and during week 3 to allow any troubleshooting and ensure that participants are filling in diaries and experience sampling appropriately. Telephone contact will also be made with a participant should they fail to complete mid-intervention assessments (week 3).

### Data management and statistical analysis

#### Data confidentiality and management

All participants will be given an anonymous trial identification code to use when submitting their completed assessments. A file linking the participant’s name to their identification code will be saved in an encrypted and password protected file and stored on a secure, protected server within the MRC-Cognition and Brain Sciences Unit. This file will be deleted once the final round of data collection is complete. Outcome data will be gathered remotely using online platforms (eg, Qualtrics; www.qualtrics.com) and an ESM data collection app. During periods of data collection, these data will be transferred to in-house secure servers within the MRC-Cognition and Brain Sciences Unit, University of Cambridge. The source data will be then deleted. Access to these data will be restricted to primary research team members ([name], [name], TD). Data management will be overseen by these team members. There will be no formal Data Management Committee because it is a small scale trial.

#### Statistical analysis

##### Self-rated and performance-based measures

The statistical analysis will be conducted by the trial statistician (PW) who will be blind to training condition. The analysis will be conducted on an intention-to-treat basis and a similar initial analysis is planned for (1) the primary training outcome (ie, self-rated EQ scores) and (2) secondary mental health outcomes (ie, CES-D, RCADS, STAXI-2, SDQ and WEMWBS). Analysis of covariance will be calculated to estimate the effect of training condition on outcome measures after adjusting for baseline performance and grouping stratification variables. This model will be calculated for our primary end-point, that is, post intervention (ie, postintervention outcome adjusted for baseline score). This model will additionally be calculated for our mid-intervention time point (ie, mid-intervention outcome adjusted for baseline score) and post intervention. There are no planned interim analyses. If a subset of items of a measure (<20% within-measure missing data), a total score will be calculated using the mean score across the non-missing items; an approach we have reported elsewhere (www.osf.io/d6y9q). Otherwise, the score for that measure will be noted as missing. We will assume that data will be missing at random and address this using standard imputation approaches in R (R Core Team, 2013).

##### ESM analysis

Only participants who completed at least 33% of the ESM questionnaires will be included in the analyses, in line with ESM guidelines.^50^ Statistical analyses will be performed using hierarchical linear models. These models are especially suited to deal with dependency inherent in the data due their hierarchical structure: ESM observations (level 1) nested within individuals (level 2). Potential confounders will be included in the model as covariates. First, a linear growth model will be estimated to assess the effect of condition (decentering training vs active control) on decentering skills over time (ie, the duration of the intervention). Second, time-lagged analyses will be performed to evaluate if higher self-rated decentering skills when confronted with a momentary psychological stressor (time=n) predict significantly lower negative affect ratings at a later time point (time=n+1). We will also control for momentary negative affect ratings (at time=n). Random intercepts and random slopes models will be estimated. In hierarchical linear models, the fixed effects reflect the overall association between a predictor and the outcome of interest, whereas the random effects reflect individual differences in this association.

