**Methods and analysis:**

Adolescents, recruited from schools in the UK and Ireland (n=57 per group, age range=16–19 years), will be randomised to complete 5 weeks of decentering training, or an active control group that will take part in a combination of light physical exercise and cognitive training. The coprimary training outcomes include a self-reported decentering inventory (ie, the Experiences Questionnaire) and the momentary use of decentering in response to psychological stressors, using experience sampling. The secondary mental health outcomes will include self-reported inventories of depression and anxiety symptoms, as well as psychological well-being. Initial statistical analysis will use between-group analysis of covariance to estimate the effect of training condition on self-rated inventories, adjusted for baseline scores. Additionally, experience sampling data will be examined using hierarchical linear models.

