#### Decentering outcome measures

The primary training outcome measure is self-rated decentering as measured using the EQ. A secondary decentering outcome measure is the self-rated use of psychological decentering in response to psychological stressors as measured using ESM. These measures have been included to address research questions 1a and 1b, respectively.

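### The 33% ESM completion rule drops randomised participants on post-randomisation response, can bias the arm comparison, and discards data that the chosen model could use

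*Protocol article*

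**What the plan says.** The ESM analysis subsection of the protocol article sets the analysis set: "Only participants who completed at least 33% of the ESM questionnaires will be included in the analyses". It gives conformity with ESM guidelines as the reason. The first model it then describes is a between-arm comparison: "a linear growth model will be estimated to assess the effect of condition (decentering training vs active control) on decentering skills over time". No ESM analysis of all randomised participants, and no sensitivity analysis without the threshold, is stated.

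The preceding subsection, on self-rated and performance-based measures, takes a different line: "The analysis will be conducted on an intention-to-treat basis and a similar initial analysis is planned for" the Experiences Questionnaire (EQ) and the mental health inventories. On missing values it adds: "We will assume that data will be missing at random and address this using standard imputation approaches in R".

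Two other sections fix the timing. Under ESM decentering items, prompts go out four times daily over a 5-day baseline and the 5 weeks of training. Under Allocation, participants are randomised after the baseline assessment.

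The rank of the ESM outcome varies. The abstract says: "The coprimary training outcomes include a self-reported decentering inventory (ie, the Experiences Questionnaire) and the momentary use of decentering in response to psychological stressors". The section on decentering outcome measures says: "A secondary decentering outcome measure is the self-rated use of psychological decentering in response to psychological stressors as measured using ESM".

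**The concern.** Randomisation makes the arms comparable as allocated. A filter on how many prompts a person later answers can undo this, because answering is behaviour that the assigned programme may influence.

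The article gives reasons not to take equal response for granted:
- The arms do different tasks: audio exercises in one, stretches and games in the other.
- One app prompts both the daily exercise and the ESM items, so someone who disengages from the programme may also stop answering.
- Participants are discontinued if serious health difficulties require intervention. If this happens early, the rule deletes all their ESM data, so removal can be related to outcome.
- The article itself lists weak adherence under remote delivery as a limitation.

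At stake is the answer to research question 1b, which sits under the primary aim. The filter is also not needed for fitting: a hierarchical model accepts unequal numbers of observations per person.

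**Working it through.** **The plan's own figures.** The article gives no power figure for ESM. Its total of 90 for the EQ (f=0.3, α=0.05, 80% power) reproduces, with power 0.804. Allowing for 20% attrition, 90/0.8 = 112.5, which rounds up to 113, or 114 with equal arms (57 each). So 114 is the number randomised.

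**How many prompts the rule requires.** The article does not say whether prompts go out at weekends or whether the 33% counts baseline prompts, so all four cases are shown. Baseline is 4 × 5 = 20 prompts.

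| Case | Prompts | Needed (33%, rounded up) | Training days needed, full response | Training days needed, 60% response |
|---|---|---|---|---|
| Daily, baseline counted | 4 × (5+35) = 160 | 53 | (53−20)/4 = 8.25 | (53−12)/2.4 = 17.1 |
| Weekdays, baseline counted | 4 × (5+25) = 120 | 40 | (40−20)/4 = 5.0 | (40−12)/2.4 = 11.7 |
| Daily, training only | 4 × 35 = 140 | 47 | 47/4 = 11.75 | 47/2.4 = 19.6 |
| Weekdays, training only | 4 × 25 = 100 | 33 | 33/4 = 8.25 | 33/2.4 = 13.8 |

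At 60% response a person answers 0.6 × 4 = 2.4 prompts a day and 12 at baseline. Early leavers are thus removed although they hold baseline records and one or more weeks of training records.

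**Participants lost.** The share failing the rule is not given. If 10%, 20% or 30% fail, 103, 91 or 80 of 114 remain.

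**Possible bias, true arm difference zero (all inputs assumed).** Let response propensity correlate r with outcome within an arm, and remove the lowest 20% of responders. The retained mean shifts by r × φ(z)/0.8, with z the 20th percentile of the standard normal: 0.280/0.8 = 0.35, so 0.35r.
- Same rate and same r in both arms, or r = 0: difference about 0.00 SD.
- 20% removed in both arms, response tied to outcome in one arm only: about 0.10 SD (r = 0.3) to 0.17 SD (r = 0.5).
- Same r in both arms, unequal removal: 0.05 SD (25% v 15%, r = 0.3), 0.09 SD (30% v 10%, r = 0.3), 0.15 SD (30% v 10%, r = 0.5).

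**Growth model under missing-at-random dropout (simulation, true difference zero).** Settings: 20 prompts in the baseline block and in each of 5 weeks; 70% response; dropout dependent on the last observed weekly mean in the decentering arm only; threshold 40 of 120. The rule removed 18% of the decentering arm and 12% of control. Units are between-person SDs of starting level.

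| Quantity | All data | After the 33% rule |
|---|---|---|
| Arm difference at week 5 (SE 0.02) | −0.01 | +0.24 |
| Arm difference in slope per week (SE 0.003) | 0.00 | +0.01 |

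Of the +0.24, about 5 × 0.011 = 0.05 comes from the slope. The remaining 0.18 or so is a difference at time zero, before any training, created by the selection. In this setting the rule disturbs levels far more than slopes.

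**The case against.** **The rule is a disclosed field convention.** It is prespecified, identical in both arms and attributed to guidelines. That stands as an answer to any charge of carelessness. The guideline is not at hand and may well support 33% as a data-quality standard, but a data-quality standard does not preserve a randomised comparison.

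**The bias is not shown.** This stands. It needs low response to be related to outcome and to act differently between arms, and the article supplies neither fact. The anticipated 20% attrition belongs to the EQ calculation and is not a forecast of failures under the ESM rule. The planned contrast is change over time, and the slope barely moved in the simulation.

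**Stronger readings that the article does not support.** A reader might infer any of the following:
- *That the rule contradicts an intention-to-treat commitment for ESM.* The statement "The analysis will be conducted on an intention-to-treat basis" sits under the self-rated and performance-based measures; the ESM subsection makes no such claim. The rule departs from the stance taken there and is not a word-for-word contradiction.
- *That the ESM comparison becomes per-protocol.* The rule counts answered prompts. Programme adherence is tracked separately, through workbooks, task completion and diaries.
- *That the ESM baseline is ignored and the minimisation factors are left out.* The first rests only on a parenthesis describing the time axis. On the second, "Potential confounders will be included in the model as covariates" does not exclude sex or CES-D. An article may leave both details to the full protocol or analysis plan.
- *That the trial's main result is at risk.* The EQ analysis, on which power rests, is untouched, and the ESM outcome is called secondary in one place and coprimary in another.

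**Conclusion.** The point holds in limited form. A stated rule removes randomised participants from a between-arm analysis mainly on post-randomisation response, and no analysis of all randomised participants is stated beside it. This departs from the intention-to-treat stance taken for the self-rated measures and can bias the comparison. The illustrations run from nil to 0.17 SD in the truncation calculation; in the simulation they are +0.24 in week-5 level and about +0.01 per week in slope. All rest on assumed inputs, so none is an estimate for this trial.

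The loss of usable data is certain for anyone who falls below the threshold. With baseline counted, that includes a full responder who stops before about training day 9 (daily prompting) or before completing 5 training days (weekday prompting). The hierarchical model could use those records under the missing-at-random assumption already made for the inventories.

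This is worth correcting because the remedy is simple and the outcome serves the primary aim. It does not invalidate the trial.

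**What to change.** In the ESM analysis subsection, define the main growth model on all randomised participants with at least one ESM record, analysed by assigned arm. Keep the 33% rule as a sensitivity analysis, state whether its denominator includes the baseline prompts, and report by arm how many participants fall below it.

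The cost is analysis wording only, with no added data collection. The ESM set can then hold up to 114 participants, against 91 if 20% were to fail the rule. The small downside is that sparse responders give noisier person-level estimates, which the model down-weights. The main analysis would still rely on missing at random, which the retained sensitivity analysis does not test.
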